#### Supervised machine learning (ML).

Supervised machine learning predictive models will be implemented using the features such as demographic information, blood biomarkers and QST scores of the study participants. Multiple ML predictive models will be developed and tested to assess their performance and efficacy to better predict which participants will be prone to develop BFNP. The predictive models will be trained/validated and tested using information available 2–3 weeks after surgery and data collected at 6–9 months post-surgery. Our implementation of supervised ML predictive models incorporates these steps: 1) A dataset is gathered. The development dataset needs to be representative of the real-world population and must include reasonably large representations of both BFNP and non-BFNP subjects. 2) Quality controls are applied. All data are subjected to a series of tests to ensure the information is valid and the data do not contain anomalies arising from measurement errors. 3) The features to be used for the prediction models are extracted from the development dataset. The feature extraction will be carried out to transform multiple data types into numerical features usable for ML model training. 4) Feature Selection: Using the domain knowledge and ML based feature selection algorithms, the number of input features will be reduced to decrease computation time and to prevent model overfitting.

A specific ML methodology is selected. We have used a variety of machine learning methodologies including Elastic Net (ENET). ENET is a flexible methodology that, based on how penalty functions are set, can implement various specific methodologies such as Least Absolute Shrinkage, Selection Operator (LASSO) and ridge regression. The algorithm performs both feature selection and regularization to enhance the prediction accuracy and interpretability of the statistical model it produces. Support Vector Machines, K-Nearest Neighbors, Random Forest and Gradient Boost are also used in the methodology on the same training/validation/test dataset, to provide comparison points when establishing the performance of the algorithms generated using ENET. Data split is performed. The model is trained and tested using 70/30 split between training (and validation) and testing datasets. The split is stratified so that training and test subsets have the same proportion of BFNP and non-BFNP class labels as that of the input dataset.

Nested Cross-Validation is performed. Cross-validation provides a way to estimate algorithm performance on an unseen (validation) dataset, using the annotated train/validate dataset in hand. To overcome bias in model performance evaluation, we will use nested cross-validation. We intend to use 10-fold cross-validation (outer-loop) to evaluate model performance and 5-fold cross-validation (inner loop) for model and hyperparameter optimization. In the outer loop 10-fold cross-validation, the original train dataset is randomly portioned into 10 equal-size subsamples. Within the 10 subsamples, a single subsample is considered to be the “validation” group, and the other 9 subsamples (the “train” group) are used for model and hyperparameter optimization. The 10-fold cross-validation procedure involves fitting a model on “train” group and evaluating the fit model on the “validation” group (outer loop). The “train” group is then provided the hyperparameter optimization scheme to find an optimal set of hyperparameters for the model (inner loop). The evaluation of each set of hyperparameters is performed using 5-fold cross-validation that splits up the provided train dataset into 5 folds. In this step (inner loop) we also evaluate settings in terms of their alignment with domain knowledge. The performance of the final model will be assessed on the test data. To estimate variance in model performance and to mitigate selection bias in training/validation/test data, the entire workflow will be repeated 100 times and, during each iteration, the model will be trained with a unique random number of seed. The average of 100 models will be used to estimate model confidence and to extract feature importance. When ML analysis of in-house data reveals patterns in alignment with domain knowledge reported in literature, this indicates the ML-trained algorithm is reflective of underlying phenomena and not overtrained on our dataset.

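### Feature selection is listed before the 70/30 split and outside the nested loops, so if it uses the BFNP label test performance is optimistic; agreement with the literature is no check on this

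*Protocol article*

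**What the plan says.** All of this stands in the protocol article, under Supervised machine learning (ML). Four numbered steps come first: gather the data, apply quality control, extract features, select features. Of extraction it says "The features to be used for the prediction models are extracted from the development dataset". The fourth step reads "4) Feature Selection: Using the domain knowledge and ML based feature selection algorithms, the number of input features will be reduced". Unnumbered text then covers the choice of learning method, and after that comes "Data split is performed. The model is trained and tested using 70/30 split between training (and validation) and testing datasets". The split concerns the labelled input data: "The split is stratified so that training and test subsets have the same proportion of BFNP and non-BFNP class labels".

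The nested cross-validation is described next. The 10-fold outer loop estimates performance; the inner loop is "5-fold cross-validation (inner loop) for model and hyperparameter optimization" and also weighs settings by how well they agree with domain knowledge. Feature selection is assigned to neither loop. For the reported result, "The performance of the final model will be assessed on the test data", and the whole procedure is run 100 times with different seeds.

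The section closes by saying that when the patterns found agree with the literature, "this indicates the ML-trained algorithm is reflective of underlying phenomena and not overtrained on our dataset".

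**The concern.** A held-out set measures performance honestly only if nothing about its patients' outcomes has shaped the model. Read in the printed order, features are selected when no test set yet exists, and nothing restricts that step to training data. A label-guided selection would then use the outcomes of the later test patients. The nested loops operate on the training portion after the feature list has been fixed, so they cannot undo this.

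The closing sentence offers agreement with the literature as reassurance against overfitting. That agreement would look the same whether or not the test result was contaminated. The Introduction presents an early biosignature for BFNP susceptibility as what the study should deliver, and this section is where its predictive performance is to be measured. An inflated AUC could make a noise signature look clinically useful.

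**Working it through.** **1. Size of the dataset.** From the Sample size section: 213 / (1 − 0.20) = 266.25, or 267 rounded up, against the stated 265 (a trivial difference). Completers: 265 × 0.80 = 212. The stated 53 BFNP patients equal both 265 × 0.20 and 212 × 0.25. Among completers the BFNP count is therefore between 212 × 0.20 = 42.4 and 53. The test set has 0.30 × 212 = 63.6, about 64 patients, of whom 0.30 × 42.4 = 12.7 to 0.30 × 53 = 15.9 have BFNP, so about 13 to 16.

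**2. Why the order matters.** For any feature, let D be the BFNP minus non-BFNP mean difference in all patients. With a stratified 70/30 split, D = 0.7 × D(train) + 0.3 × D(test), and over random splits the average of D(test) is D itself. Selecting features because |D| is large therefore guarantees, on average, a difference of the same sign in the test set, even when every feature is noise. It also shows why repetition does not help: averaging over 100 splits converges on D, which is the quantity that was selected on. If selection is rerun in each repeat but still before the split, nothing changes.

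**3. Size on pure noise.** Outcome unrelated to any feature, so the true AUC is 0.50; t-test filter; stratified 70/30 split; AUC on the test part. The article gives no number of candidate features, so a range is shown.

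With 212 patients, 53 BFNP and 20 features kept:

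| Candidates (assumed) | Selection before split | Selection in training only |
|---|---|---|
| 50 | 0.65 | about 0.50 |
| 500 | 0.84 | about 0.50 |
| 5,000 | 0.92 | about 0.50 |
| 20,000 | 0.95 | about 0.50 |

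A separate run of this setting, with a ridge model on the selected features, gave 0.64, 0.83, 0.92 and 0.94, against 0.50 to 0.51 with selection in training.

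With 212 patients and 42 BFNP (test set 64, 13 BFNP), ridge model:

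| Candidates (assumed) | Kept | Selection before split | Selection in training only |
|---|---|---|---|
| 30 | 10 | 0.63 | 0.50 |
| 100 | 20 | 0.74 | 0.51 |
| 1,000 | 20 | 0.89 | 0.51 |
| 20,000 | 20 | 0.96 | 0.50 |

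The direction does not depend on the assumptions; the size does, chiefly on the number of candidates. Large counts are possible because the blood collection section plans RNA sequencing, but the article does not say how many transcripts would reach the selection step.

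**4. The literature check.** Domain knowledge enters three times: in selecting features, in judging inner-loop settings, and in the closing sentence as evidence. The third use partly reads back what the first two put in. Overfitting is a gap between performance on the data used and on untouched data, and agreement with publications does not measure that gap.

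**The case against.** The best defence is that printed order need not be execution order. The numbering stops at four, and the later prose is not strictly chronological: it mentions the comparison learners working on the training, validation and test data before it mentions the split. The selection step names no dataset and does not say that it uses the BFNP label. Reduction by domain knowledge or by label-blind filters would cause no such bias. Elastic net, the lead method, does its own selection, which is clean when fitted on training data. The article is condensed, and it does fix real protections: a stratified held-out test set, nested cross-validation, regularisation and final assessment on test data.

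Much of this stands, and it limits the point. A reader might infer that selection on the full labelled dataset is planned and contamination certain. The text does not support that, since neither the dataset nor the use of labels is stated for this step. A reader might also infer that literature agreement is taken as proof; the article says only that it indicates. Nor does the inner-loop agreement criterion bias held-out performance, because it acts within training data. Finally, the group comparisons for the two primary aims use growth mixture models and do not depend on this pipeline.

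What the defence does not remove is that the article prints an order and the contents of both loops, and on that description selection lies outside every safeguard. Elastic net's internal selection does not cover a separate, earlier step. The closing inference is unsound on any reading.

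**Conclusion.** The point holds conditionally. If the steps are run as listed and the selection is guided by the BFNP label, test AUC is biased upward: on noise, to about 0.65 with 50 candidates and 0.84 to 0.95 with 500 to 20,000, instead of 0.50. This assumes about 212 completers with 53 BFNP, a t-test filter and 20 features kept; even 30 candidates with 10 kept gave 0.63. Neither the nested loops nor the 100 repeats correct it. Separately, and without any condition, agreement with the literature is not evidence against overtraining, and here it is partly circular. Both are faults in what is written rather than omitted detail, and they should be corrected before any model is built.

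**What to change.** State that the split comes first. Place all outcome-guided feature selection, and any other data-driven preprocessing, inside the training folds, redone in each outer fold and in each of the 100 repeats. Before the split allow only label-blind filters or a feature list from the literature fixed in advance.

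Remove the inference from literature agreement to absence of overtraining. Judge overfitting by performance on untouched held-out data, and add a run of the whole procedure with permuted BFNP labels, which should return an AUC near 0.50. The inner-loop agreement criterion may stay, provided that agreement with the literature is then not cited as evidence against overfitting.

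The cost is code order, wording and some extra computing time; the reported AUC will probably be lower. Data collection is unaffected. The Study design section says no analysis has yet been implemented, and 64 of the planned 265 fracture patients were enrolled at the stated status date, so the change can be made cleanly now.

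### Inner-loop settings are chosen partly for agreement with domain knowledge, which can tilt the signature toward known markers, so that agreement cannot show that the model is not overtrained

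*Protocol article*

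**What the plan says.** All of this stands in the protocol article, Statistical analysis, under Supervised machine learning (ML).

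- The nesting: "We intend to use 10-fold cross-validation (outer-loop) to evaluate model performance and 5-fold cross-validation (inner loop) for model and hyperparameter optimization".
- The predictive criterion: "The evaluation of each set of hyperparameters is performed using 5-fold cross-validation that splits up the provided train dataset into 5 folds".
- The added criterion, two sentences further on in effect and in the same step: "In this step (inner loop) we also evaluate settings in terms of their alignment with domain knowledge".
- Repetition: "the entire workflow will be repeated 100 times and, during each iteration, the model will be trained with a unique random number of seed". Feature importance is then taken from the average of the 100 models.
- The closing inference, for the case where the patterns found agree with what the literature reports: "this indicates the ML-trained algorithm is reflective of underlying phenomena and not overtrained on our dataset".
- Prior knowledge also enters earlier, at feature selection: "Using the domain knowledge and ML based feature selection algorithms, the number of input features will be reduced".

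Elastic net is the main method, with four comparators: "Support Vector Machines, K-Nearest Neighbors, Random Forest and Gradient Boost are also used in the methodology on the same training/validation/test dataset". Performance is assessed on the outer validation folds and on a 30% stratified test set.

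**The concern.** An inner loop picks the setting that predicts best on data not used to fit it. Here a second consideration takes part in that choice, and it concerns what the model contains, not how well it predicts. Two things are at stake.

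**Content of the signature.** The Introduction states that the study should identify a set of biomarkers for early susceptibility to BFNP. If candidate settings score about equally and the more familiar one is preferred, markers already in the literature gain an advantage that the data did not give them, and new markers lose by the same amount. Averaging over 100 repeats does not remove this, because the preference acts in the same direction in every repeat.

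**Meaning of agreement with the literature.** The same section selects for agreement and then reads agreement as support for the model. Once agreement has been selected for, it is no longer independent evidence.

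**Working it through.** The plan gives no figure for this criterion, so there is none to reproduce. The check asks whether the criterion can matter at this sample size, and which results it would affect.

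**1. Patients and events per fold.** Inputs: 213 evaluable patients (Sample size); 20% BFNP (a 1:4 group ratio, and 53 of 265); 70/30 split, 10 outer and 5 inner folds (machine-learning section).

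- Training set: 213 × 0.70 = 149 patients; 149 × 0.20 = 30 with BFNP.
- Outer validation fold: 149 / 10 = 15 patients, 3 with BFNP.
- Inner fold: 149 × 0.90 / 5 = 27 patients, 5 with BFNP. With one in four developing BFNP, about 7.

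**2. Noise in the inner score.** With no signal, the standard error of an AUC is √[(n1 + n0 + 1) / (12·n1·n0)]. For n1 = 5 and n0 = 22 this is √(28 / 1,320) = 0.146 per fold. Averaged over five folds, treated roughly as independent, it is 0.146 / √5 = 0.065. Competing settings are scored on the same patients, so their scores are correlated and differences between them vary less than this. Differences of one or two hundredths still say little.

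**3. Does the criterion change what is selected?** Illustrative null simulation; every input below other than the 213 patients and the 70/30 split is an assumption or follows from the 20% above.

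- 213 patients, 43 events, 50 pure-noise features, 10 of them labelled known (chance share 10 / 50 = 0.20).
- 20 candidate settings, each a random subset of 25 features from which the 8 with the largest group difference are kept.
- 149 training and 64 test patients, 5-fold cross-validation within training, 300 runs. The outer 10-fold loop was not simulated.

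| Rule for choosing the setting | Known-marker share | Cross-validated AUC of chosen setting | Test AUC |
|---|---|---|---|
| Best cross-validated AUC | 0.197 | 0.598 | 0.497 |
| Most aligned of the five best | 0.291 | 0.579 | 0.495 |

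Standard errors are about 0.007 for the shares and 0.005 to 0.006 for test AUC. The share rises by 0.291 − 0.197 = 0.094, or from about 1.6 to 2.3 of 8 markers, at a mean cost of 0.598 − 0.579 = 0.019 in inner AUC. Test AUC stays at chance under both rules.

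**4. Could the check be made by eye?** 100 repeats × 10 outer folds = 1,000 inner-loop selections per algorithm, or 5,000 for five algorithms. Judgement by a person in each is not practicable; a coded rule is.

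**5. The two statements together.** Inner loop: settings are evaluated partly for agreement with domain knowledge. End of the section: agreement with the literature indicates no overtraining. The simulation shows why the second does not follow. The aligned model had a raised share of known markers and a test AUC of 0.495, so it agreed more with prior knowledge and predicted nothing.

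**The case against.** The strongest reply is that the article describes a legitimate use of prior knowledge. With roughly 43 to 53 BFNP cases, such knowledge can stabilise a model, and if known markers do carry signal it may improve prediction. The alignment check is an addition to cross-validation, and nothing says that it overrides it; it may be only a tie-break. A marker list or an overlap score could run automatically on training data in every inner loop. The outer folds and the 30% test set would then still give an honest estimate, as step 3 shows. The score, its weight and the marker list are details that an article may leave to the analysis plan. All of this stands, and the absence of those details is not the point here.

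A reader might go further and infer that a person judges alignment, that the criterion cannot run inside the loop, that it would be applied once by analysts who have seen everyone's results, or that familiar settings win over better-predicting ones. The documents support none of these. They do not say who or what judges alignment, they place the check in the inner loop, and they give no order of precedence. The nesting would fail only under ad hoc judgement or judgement on results from all the data.

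The reply does not reach two things. A non-predictive criterion, however well coded, can shift signature content when scores are close. And agreement that took part in selection cannot afterwards count as independent support.

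**Conclusion.** The point holds in a limited form. The stated rule adds a criterion that does not measure prediction to a choice made on about 27 patients and 5 BFNP cases per inner fold (213 evaluable, 20% BFNP). It can therefore decide the choice and move the signature toward known markers without any signal.

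The size of the shift, 0.197 to 0.291, belongs to the assumed features, marker list and rule. A pure tie-break would shift less and a heavier weight more. The direction does not depend on those inputs.

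The documents do not show that the performance estimate is biased, and a fixed coded rule would not bias it. What fails whichever way the rule is implemented is the closing inference: agreement with the literature is partly built in by selection and cannot show that the model is not overtrained. No sample size or power figure is affected.

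**What to change.** - Choose inner-loop settings by one numeric out-of-fold score, for example log-loss or AUC, computed automatically in every fold and repeat.
- If prior knowledge is to be used, enter it only as a fixed, coded prior set before the data are seen, and run it on training data alone.
- Compare the locked signature with published markers afterwards, as description only.
- Remove the inference from agreement to absence of overtraining, and rest any such statement on held-out performance.

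This is a change of wording in the protocol or analysis plan; no visit, procedure or sample size changes. The article says that no analysis has been implemented, so the change can still precede results. The small downside is that the selected model may look less familiar biologically.

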### Ethical considerations

This study protocol was approved by the IU Institutional Review Board (**IRB 19914**). Informed consent will be obtained from all participants or their legal guardians. All methods are performed in accordance with relevant guidelines and regulations.

Participation in this study is voluntary. Before choosing to participate in the study, participants will be able to discuss any concerns they may have with the study team including time commitment, testing procedures, potential expenses, and side effects. The participants may choose to decline to be part of the study, and they do not have to participate or may withdraw from the study at any time. Leaving the study early will not result in any loss of benefits that they already have.

#### Risks and safety.

There are risks to participating in any research study. There is a risk of side effects from the procedures performed during this study. Side effects may vary from person to person. Possible risks include:

**Blood draw**. The risks of drawing blood from a vein include discomfort at the site of puncture; possible bruising and swelling around the puncture site; rarely, an infection; and uncommonly faintness from the procedure. Risks can be reduced by using sterile needles, alcohol scrub, applying pressure to arm after we remove the needle, and using a trained technician experienced in collecting research blood draws.

**Quantitative sensory testing**. During the study session, participants may feel pain. This is intended because this is a pain study. However, in any of the pain tests, participants are not expected to experience severe pain as the temperatures and pressures used are below pain tolerance levels observed in human studies. The pain they experience from these pain tests is temporary and generally diminishes immediately after the pain test. They may also stop any pain test at any time with no adverse consequences. Below is a description of the types of pain testing the participants will experience in this study.

a. **Heat pain from the thermode**: Several things may occur in the skin area (1 inch square) after the heated probe makes contact with the skin: (1) It may turn red like a mild sunburn and (2) there may be a slight burning feeling after the heat is removed. For most people this is gone in 1–2 minutes. It may take up to 1–2 hours for all the symptoms to disappear. In addition, during this thermal sensitivity testing, the participant has a button control that can stop the process at any time if the pain becomes intense.b. **Cold Pain from the thermode**: When the temperature of the small metal probe touching the skin decreases, the coldness that the subject experiences may become painful and unpleasant. The subject’s skin may turn red for a short period of time. However, the risk associated with this procedure is low because the temperature of the probe will not reach temperatures that will cause blisters or skin freezing.c. **Pressure/mechanical pain**: The handheld probe that has a small nylon tip is applied just to the point of making a slight indentation without puncturing the skin. When the probe is used to tap the skin ten times in a row, participants may stop this test at any time if it becomes too painful. The pain is temporary, and this procedure will not damage skin. The pressure tool has a flat, rubber tip and will not reach a pressure level to damage tissue. There is a slight chance that a small bruise may form as a result of the pressure pain. If a bruise should appear it is usually short lasting and not painful.d. **Cold water pain**: While the cold water is perceived as unpleasant, the temperature will be monitored to ensure it remains at appropriate temperatures used successfully in other studies. In addition, the participants can remove their hand(s) from the cold water at any time if the pain becomes too intense.

**Images of ankle taken with thermal camera.** The camera used to take thermal pictures of the participant’s ankle is a non-invasive tool. There is no radiation exposure, no compression of ankles, and no physical risks associated with this procedure.

**Psychological discomfort.** The prospect of being subjected to painful stimulation in an unfamiliar laboratory, surrounded by unfamiliar investigators and equipment that may look intimidating may lead to anxiety. The researchers try to minimize this anxiety by thoroughly explaining all procedures to the participants and taking the time to answer all their questions. In addition, the pain tests always start with a few non-painful stimuli before the temperature or pressure rises gradually. Despite these measures, it is not possible to completely rule out that participants may feel some anxiety during the first session. However, this anxiety should lessen during the second and subsequent sessions, once a participant has become familiar with the experimental procedures.

**Risk of possible loss of confidentiality.** The study team will collect information about the participants from their medical records. This information, some of which may identify the participants, may be used for research-related purposes. This may include making sure the participants meet the criteria to be in this study, gathering information about their medical history to include in the research data, reviewing results of their medical tests for safety purposes, checking on their health in the future to help answer our research question, or to inspect and/or copy their research records for quality assurance and data analysis. There is a risk of possible loss of confidentiality, which means there is a risk someone outside the study team could get access to patient research information from this study. Individuals and organizations including the researchers and research staff on this study, the IU Institutional Review Boards or its designees, the IU Clinical Research Center (ICRC), the US governments or agencies as required by law, the data safety monitoring boards, State or Federal Agencies with research oversight responsibility including but not limited to Office for Human Research Protection (OHRP) and Department of Defense (DOD; Office of Human Research Oversight [OHRO]).

*Biological specimen*, e.g., processed blood sample, will be stored and labeled only with a number identifier. No subject name or personal information will be on this label.

Information and specimens collected for this study may be used for other research studies or shared with other researchers for future research. If this happens, information which could identify the participants, such as names and other identifiers, will be removed before any information or specimens are shared. Since identifying information will be removed, we will not ask for additional consent.

